# Effects of transcutaneous electrical nerve stimulation (TENS) on arterial stiffness and blood pressure in resistant hypertensive individuals: study protocol for a randomized controlled trial

**DOI:** 10.1186/s13063-016-1302-8

**Published:** 2016-03-29

**Keywords:** Arterial stiffness, Resistant hypertension, Sympathetic system, Blood pressure, Transcutaneous electrical nerve stimulation

## Abstract

**Background:**

Resistant hypertension (RH) treatment requires an adequate and intense therapeutic approach. However, the results are not always satisfactory despite intensive treatment. Of the different pathophysiological mechanisms involved in the pathogenesis of RH, sympathetic overstimulation and therapies that block the sympathetic system have been widely studied. These approaches, however, are invasive and expensive. Another possible approach is by transcutaneous electrical nerve stimulation (TENS), a noninvasive method that modulates activity by using low-frequency transcutaneous electrical stimulation to inhibit primary afferent pathways. Thus, the current study will evaluate the effect of applying TENS in the cervicothoracic region of subjects with RH and will seek to develop a new low-cost and readily available therapy to treat this group of hypertensive individuals.

**Methods/design:**

This is a randomized, single blind (subject), parallel-assignment study controlled with a sham group and including participants aged 40 to 70 years with resistant hypertension. The trial has two arms: the treatment and control (sham group). The treatment group will be submitted to the stimulation procedure (TENS). The sham group will not be submitted to stimulation. The primary outcomes will be a reduction in the peripheral blood pressure and adverse events. The secondary outcomes will be a reduction the central blood pressure. The study will last 30 days. The sample size was calculated assuming an alpha error of 5 % to reject the null hypothesis with a statistical power of 80 %, thereby resulting in 28 participants per group (intervention versus sham).

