## Methods/design

### Design

The present trial (clinicaltrials.gov identifier: NCT02365974, registered on 8 February 2015) will be a randomized, open-label, parallel-assignment study controlled with a sham group. All patients who participate in the research will sign informed consent forms. The project design, approved by the Research Ethics Committee of FAMERP, São Paulo, Brazil, which is accredited by the Office of Human Research Protections as an Institutional Review Board (CAAE n° 07606212.5.0000.5415, n° 94.248/2012) (Additional file 1), will comply with the following described criteria.

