### Random allocation

A computer-validated software program (Random Allocation) will be used for the random allocation. The study coordinator will organize and number the envelopes, which will be allocated in order of patient enrollment. The professional responsible for the Endo-PAT procedure and evaluation of arterial stiffness parameters will be blinded.

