### Randomization and follow‐up

#### Protocol

Patients will be divided into two groups: treatment and control (sham group). The sham group will be submitted to the procedure to fit the stimulation equipment. However, these patients will not be submitted to stimulation. Both groups will undergo a physical examination at the start and end of the study period to determine anthropometric variables. The BMI, defined as the weight (kg) divided by the patient’s height squared (m^2^), will be calculated. The height will be determined in centimeters using a measuring tape while the individual stands in bare feet. Individuals with a BMI < 25 kg/m^2^ will be classified as normal, overweight as a BMI between 25 and 30 kg/m^2^, and obese as a BMI ≥ 30 kg/m^2^. The waist circumference will be measured using a measuring tape at half the distance between the iliac crest and the lower costal margin. Patients will undergo the following tests before and after the end of the 4-week study period: 24-h ambulatory blood pressure monitoring (ABPM), 24-h dynamic electrocardiography, continuous measurement of beat-to-beat BP, endothelial function measurement (Endo-PAT 2000), and radial artery applanation tonometry (AT). Table 1 shows a summary of the key practical aspects of the study with all follow-up visits and requested exams, and Fig. 1 represents the flowchart of the study.

**Table 1 Tab1:** Key practical aspects of the study with all the clinical visits and the requested exams

Visits	Screening	1^st^ week	2^nd^ week	3^rd^ week	4^th^ week
Weeks	−1	1	2	3	4
Informed consent	X				
Inclusion and exclusion criteria	X	X			
Medical history	X				
Medical evaluation/physical examination (BP measure)	X	X	X	X	X
Randomization		X			
Application of TENS (3x/week)		X	X	X	X
Creatinine	X				X
Fasting glucose	X				X
Glycated hemoglobin	X				X
Potassium	X				X
Uric acid	X				X
Insulin	X				X
Total cholesterol	X				X
HDL-c	X				X
Triglycerides	X				X
Urinary sodium	X				X
Urinary potassium	X				X
Microalbuminuria	X				X
GFR estimation	X				X
Specific biochemistry tests		X			X
Ambulatory blood pressure monitoring		X			X
24-h electrocardiographic monitoring		X			X
Evaluation of sympathetic activity		X			X
Evaluation of endothelial function		X			X
Evaluation of arterial stiffness		X			X

*BP* Blood pressure, *TENS* transcutaneous electrical nerve stimulation, *HDL-c* high-density lipoprotein cholesterol, *GFR* glomerular filtration rate

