### Application of TENS

TENS will be applied in the cervicothoracic ganglion region located between the C7 and T4 vertebral processes for 40 min three times weekly for a total of 4 weeks.

Electrostimulators (Endomed 684, Enraf Noniuns, Rotterdam, Netherlands) with two 80-Hz output channels at a pulse width of 150 μs will be used for the application of TENS. The intensity in milliamps (mA) will be adjusted depending on the sensitivity of each individual patient. This electrical stimulus has a high-frequency current that will cause mild local paresthesia without causing pain or unpleasant sensations. The intensity will be increased from zero until the perceived sensation reaches the maximum sensory threshold without pain or discomfort or involuntary muscle contractions. The 5 × 5-cm self-adhesive electrodes (Valutrode mark) are attached to the patient after marking the correct location using a dermatographic pencil and cleaning the skin. The arrangement thereof will be parallel on each side of the C7 (channel 1) and T4 (channel 2) vertebral spinous processes (Fig. 2) [58].

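### The article labels the trial both subject-blinded and open-label, and the sham as described is unlikely to keep participants reliably blinded

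*Protocol article*

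**What the plan says.** Three places in the protocol article speak to blinding.

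- Abstract, Methods/design: "This is a randomized, single blind (subject), parallel-assignment study controlled with a sham group".
- Methods, Design: the trial "will be a randomized, open-label, parallel-assignment study controlled with a sham group".
- Methods, Random allocation: "The professional responsible for the Endo-PAT procedure and evaluation of arterial stiffness parameters will be blinded".

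Two places describe what participants in each arm experience.

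- Protocol (under Randomization and follow-up), sham arm: "The sham group will be submitted to the procedure to fit the stimulation equipment". The next sentence reads: "However, these patients will not be submitted to stimulation".
- Application of TENS, active arm: "The intensity will be increased from zero until the perceived sensation reaches the maximum sensory threshold without pain or discomfort or involuntary muscle contractions". The same section expects the current to produce mild local paresthesia and sets 40-minute applications three times a week for 4 weeks.

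The primary outcome is change from baseline in peripheral blood pressure. Assessment of outcomes has office pressure taken as the mean of two readings on an automatic device.

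**The concern.** The first two statements are current text about the same trial and cannot both be right about the participant. The third settles nothing, because it concerns an assessor. A reader of the abstract and a reader of the methods would judge the risk of bias differently.

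The described procedure adds a second difficulty. One arm is adjusted by what the patient reports feeling, and the other receives nothing to feel. A sham arm is there so that expectation and attention act equally on both groups. If many participants can tell their arm, the between-arm difference in blood pressure mixes any specific effect of stimulation with a response to believing oneself treated or untreated. An automatic device limits observer influence on the reading but not the participant's own response. The Background itself notes, for invasive device therapies in resistant hypertension, that pressure fell similarly in treated and placebo groups, so non-specific responses are a live issue in this population. A report that called the trial subject-blinded without qualification would overstate what was controlled.

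**Working it through.** **1. The labels side by side.**

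| Person | Abstract | Design | Random allocation |
|---|---|---|---|
| Participant | blinded | not blinded (open-label) | not mentioned |
| Therapist applying TENS | not mentioned | not blinded (open-label) | not mentioned |
| Person measuring office BP | not mentioned | not blinded (open-label) | not mentioned |
| Endo-PAT / stiffness assessor | not mentioned | not blinded (open-label) | blinded |

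The participant row is a direct contradiction. The last row shows that an unqualified open-label description does not fit either. If participant and assessor are both blinded, the abstract's single-blind label is too narrow. If only the assessor is blinded, the abstract is wrong about the participant. The article does not say whether the blinded assessor also takes the primary office pressure.

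**2. What each arm feels.** Active: current raised from zero to a sensory ceiling, with paresthesia expected. Sham: equipment fitted, no current. For the active arm the schedule gives 3 × 4 = 12 applications. The difference lies in a sensation that the article itself predicts and uses to set the intensity.

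**3. The plan's own figure.** Inputs from Sample size calculation and Statistics: SD 8 mmHg, difference 6 mmHg, two-sided alpha 0.05, power 80%.

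n per group = 2 × (1.96 + 0.84)² × 8² / 6² = 2 × 7.85 × 64 / 36 ≈ 27.9, so 28.

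This reproduces the stated 28. The blinding question does not alter it.

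**4. Illustration under an assumed bias.** The article gives no size for an expectation effect. Assume no specific effect of TENS, a between-arm bias b due only to expectation, 28 per arm and SD 8.

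SE = 8 × √(2/28) = 2.14 mmHg.

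P(reject) = Φ(b/SE − 1.96) + Φ(−b/SE − 1.96).

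| Assumed b (mmHg) | b/SE | Normal approximation | Noncentral t |
|---|---|---|---|
| 0 | 0 | 5.0% | 5.0% |
| 1 | 0.47 | 7.5% | 7.5% |
| 2 | 0.94 | 15.5% | 15.1% |
| 3 | 1.40 | 28.9% | 28.1% |

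Biases of 2 and 3 mmHg are 2/6 = one third and 3/6 = one half of the planning difference.

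**5. What the illustration does not describe.** These are rejection rates of a two-sample t test on change. Statistics assigns the unpaired test to baseline differences and the paired test to change within the groups. It also names a Pearson correlation between pressure reduction and treatment. That would match a two-sample test only if treatment were coded as a two-level variable, which the section does not say. The table shows sensitivity to an assumption and is not an error rate of the stated analysis.

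**The case against.** The contradiction in labels has no good defence. The objections bear on how far the rest can be taken, and several stand.

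- **A reader might infer that the sham cannot keep anyone blinded.** The document does not show that. The design is parallel, so no sham patient is given the active condition for comparison, and some who have never had TENS may not guess. What patients are told is not shown. Doubtful or unlikely is supported; impossible is not.
- **A reader might infer that intensity is reset at every session, or that sham patients attend 12 silent sessions.** Both are plausible, but neither is stated. The TENS row in Table 1 does not separate the arms.
- **A reader might fault the plan for having no check of blinding.** This is a condensed article. Scripts and blinding checks commonly sit in the full protocol, so their absence here is not an error. The treatment-guess item proposed below is an inexpensive safeguard.
- **A reader might take 7.5%, 15% or 28% as the trial's false-positive rate.** The bias is wholly assumed and the test is not the one stated for change.
- **Timing.** Trial status says randomization has begun, so anything added now reaches only some participants.

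None of this removes the conflict between the abstract and the Design section, or the difference in sensation between the arms.

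**Conclusion.** The point holds and should be corrected. It is certain that the article gives incompatible statements about participant blinding, and that the methods name only the Endo-PAT and stiffness assessor as blinded. It is a reasonable inference, not a demonstrated fact, that a no-current sham set against current raised to a felt ceiling is unlikely to keep participants reliably blinded. The consequence is that the TENS minus sham difference in blood pressure may contain an expectation component of unknown size; the documents support no figure for it. Which label was intended cannot be settled from this article. The sample size is unaffected.

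**What to change.** 1. Reconcile the abstract, Design and Random allocation by listing, identically in the abstract and the methods, who is and is not blinded: participant, therapist, person measuring blood pressure, and tonometry/Endo-PAT assessor. Do not claim secure subject blinding.
2. Add one treatment-guess item to the semistructured questionnaire already described under Adverse events, at least at week 4 for the remaining participants, and report the answers by arm with the number asked.
3. State in advance that if the guesses show the blind failed, the conclusion will be limited to TENS as delivered versus no stimulation.

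The cost is wording and one question; intervention, outcome and sample size are unchanged. The downsides are a less favourable blinding claim and incomplete guess data, because patients have already been randomized.

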**Discussion:**

In recent decades, RH has become very common and costly. Adequate control requires several drugs, and in many cases, treatment is not successful. Sympathetic nervous system inhibition by renal denervation and central inhibition have significant effects in reducing BP; however, these treatments are costly and invasive. Another type of sympathetic nervous system inhibition can also be noninvasively achieved by electric current. Therefore, the application of TENS may be a new therapeutic option for treating resistant hypertensive individuals.

**Trial Registration:**

Clinical Trials NCT02365974

**Electronic supplementary material:**

The online version of this article (doi:10.1186/s13063-016-1302-8) contains supplementary material, which is available to authorized users.

## Background

### Hypertension in the context of cardiovascular disease

In Brazil, cardiovascular diseases (CVD) accounted for 30 % of deaths in 2008, with hypertension alone affecting more than 36 million people [1]. In the United States, this figure is even higher, as approximately 80 million Americans have hypertension [2].

As one of the main risk factors for the development of CVD, hypertension is the starting point of cardiovascular, cerebrovascular, and renal impairment. In most cases, by the time there is a manifestation, this disease, although still manageable, is irreversible. The main risk factors associated with hypertension are smoking, physical inactivity, stress, alcohol consumption, age, obesity, and an unhealthy diet [3], all of which can alter the integrity of the vascular endothelium and lead to a number of complications.

Currently, a broad therapeutic arsenal is available for the treatment of hypertension. Nonetheless, sometimes hypertension becomes difficult to control due to varying situations, thereby characterizing resistant hypertension (RH), which requires a more intensive therapeutic approach. RH is a condition in which the blood pressure (BP) remains above the recommended target even when treated with the maximum tolerated doses of three antihypertensive drugs with synergistic actions, including a diuretic. A condition exists that is known as controlled resistant hypertension, which is defined as high BP that is controlled using four antihypertensive drugs [4]. Although the exact prevalence of RH has not yet been precisely established, this state is estimated to occur in 12–15 % of the hypertensive population [5]. The risk factors associated with RH are similar to those of hypertension; however, it is more common in elderly patients; females; Blacks; obese patients; physically inactive patients; and those with left ventricular hypertrophy, diabetes mellitus, chronic renal disease, metabolic syndrome, and high sodium intake [4].

### Hypertension and inflammatory markers

The long-term effect of RH on the vascular system can be catastrophic. Currently, vascular abnormalities are known to exist early in the development of hypertensive diseases and may manifest as severe endothelial dysfunction.

Endothelial dysfunction is considered an early marker of vascular complications. It participates in the pathophysiology of atherogenesis, which occurs in one of the first stages of arterial disease [6, 7] as a result of risk factors that promote oxidative stress and nitric oxide (NO) inactivation [8]. Endothelial dysfunction involves several functional changes: impaired endothelium-dependent vasodilation, changes in the endothelial barrier function, inflammatory activation, and stimulation of coagulation [9]. Proinflammatory changes seem to be involved in the development of hypertension and in many other situations, including aging, diabetes, dyslipidemia, smoking, and obesity [10–13]. These changes are characterized by a series of highly specific and essentially inflammatory, cellular, and molecular responses that lead to endothelial injury. Environmental factors such as salt intake and psychosocial stress may contribute to the activation of systems that participate in the pathogenesis and progression of hypertension. Moreover, both the sympathetic nervous and renin-angiotensin-aldosterone systems have very important roles, as there are correlations between the activation of these systems and increased inflammatory activity in hypertensive subjects. Thus, hypertension seems to be associated to inflammatory disorders [13]. The inflammatory process is characterized by infiltration of macrophages and T lymphocytes in the endothelium. Activated lymphocytes and macrophages release a variety of inflammatory mediators such as cytokines, adhesion molecules, and matrix metalloproteinases (MMPs), resulting in increased inflammatory cell recruitment, the migration and proliferation of endothelial cells, platelet aggregation, and the release of free radicals [11, 14].

Several inflammatory markers, such as proinflammatory cytokines, interleukins (IL-1β, IL-6, IL-8, IL-18), and tumor necrosis factor (TNF-α) related to activated monocytes, have been identified in these situations. Elevated expressions of intercellular adhesion molecule-1 (ICAM-1) in endothelial cells [11, 15, 16] and highly sensitive C-reactive protein (hsCRP) have also been found. Recent studies show that cardiovascular risk is twice as high in patients with elevated hsCRP compared to patients with lower values. The hsCRP also has an effect on the endothelial surface as the migration and adhesion of monocytes increases, causing the synthesis of chemotactic factors due to the secretion of other proinflammatory factors, such as TNF-α, IL-6, and IL-8 [13, 17]. In addition to proinflammatory cytokines, other cytokines with anti-inflammatory activity, such as IL-10, are present.

In animal studies, IL-10 has demonstrated protective roles against the stability and formation of atherosclerotic lesions. Some clinical studies have shown that patients with acute coronary syndrome have reduced IL-10 levels compared to stable patients, raising the possibility that low levels of IL-10 may be related to atherosclerotic plaque instability [18].

Vascular endothelial dysfunction also promotes inflammation by inducing the production of vasoconstrictor agents, adhesion molecules, and growth factors, including angiotensin II (Ang II). Ang II, one of the end products of the renin-angiotensin system (RAS), is actively involved in the pathogenesis/pathophysiology of hypertension. It may be responsible for triggering endothelial dysfunction and vascular inflammation by inducing oxidative stress, a fact that results in the release of inflammatory mediators and in cell growth [12, 13, 18, 19]. Some studies have demonstrated that Ang II increases the expressions of IL-6, IL-8, IL-18, and the monocyte chemoattractant protein (MCP-1), the last of which is the main regulator of leukocyte recruitment to the vascular wall. In addition, Ang II stimulates the expression of ICAM-1 and the infiltration of macrophages independently of the increase in BP [19, 20].

The role of Ang II as a proinflammatory mediator of vascular injury is supported by the protective anti-inflammatory effects of RAS inhibitors. Among other effects, RAS inhibitors have properties that result in antithrombotic and fibrinolytic actions. The thrombogenic status mainly results from a high concentration of plasminogen activator inhibitor (PAI-1), which leads to an excessive accumulation of fibrin inside vessels, a situation that contributes to vascular events [14]. Thus, PAI-1 is considered an important regulator of thrombogenesis; increased thrombogenesis can increase the risk of atherothrombotic events and promotes the progression of vascular disease [21].

Fibrinogen, an acute phase protein, and cytokines are also directly related to vascular disease [22]. Prospective studies on healthy subjects demonstrated a direct and independent association between the plasma fibrinogen levels and the risk of coronary and cardiovascular events and mortality [16].

As previously mentioned, vascular inflammation and oxidative stress play a crucial role in the pathogenesis of vascular injury mediated by Ang II. Recently, angiotensin-converting enzyme 2 (ACE-2) was identified as having a pleiotropic effect on Ang II, resulting in the neutralization of its proinflammatory and pro-oxidant actions via receptors. Interestingly, the Ang II type-1 receptor blockers may increase ACE-2 expression and activity, thereby reducing cardiovascular and oxidative damage [23].

MMPs are responsible for the degradation of extracellular matrix proteins, breaking them down into their specific peptide bonds, including the cells of the vascular smooth muscle, endothelium, fibroblasts, and inflammatory cells [24–26]. The interaction of MMPs with their endogenous tissue inhibitors (MMP tissue inhibitors - TIMPs) is important among the factors that regulate MMP activity [27–29]. Under physiological conditions, a balance exists in the ratio of MMPs and TIMPs. However, during pathological processes such as hypertension, an imbalance occurs that leads to excessive degradation of extracellular matrix proteins [28] and, consequently, to pathological vascular remodeling. Among these proteolytic enzymes, MMP-9 has an important role in cardiovascular diseases, including atherosclerosis, coronary artery disease, vascular aneurysms, and hypertension [30–36]. Studies suggest that increases in MMP-9 activity are associated with increased arterial stiffness not only in patients with isolated systolic hypertension but also in young individuals without comorbidities [34, 36]. Notwithstanding these reports, studies are scarce that compare MMP levels with arterial stiffness markers in populations with different BP levels.

The aforementioned biochemical changes have a direct relationship with high BP, endothelial dysfunction, and increased vascular stiffness in RH patients, as is demonstrated by reduced flow-mediated vasodilation and increased pulse wave velocity (PWV), which result in higher central BP levels (CBP) [37].

